### **5.5.2 Treatment Allocation**

Treatment allocation will be as per the randomisation instruction.

### **5.5.3 Emergency Unblinding Procedures**

Not applicable.

### **5.5.4 Premature Withdrawal**

Patients have the right to withdraw from the study at any time for any reason. The Investigator has the right to withdraw patients from the study according to his/her discretion. The reason(s) for withdrawal from the study must be recorded in the CRF.

Criteria for terminating participation in the study are listed below:

1. Patient withdrawal of consent
2. Investigator’s discretion that it is in the best interest of the patient to withdraw
3. Intercurrent illness: a condition, injury, or disease that renders continuing the study unsafe or regular follow-up impossible
4. General or specific changes in the patient's condition that renders the patient ineligible
5. Termination of the clinical study by the sponsor

# **INVESTIGATIONAL MEDICINAL PRODUCT AND PLACEBO**

## **6.1 STUDY DRUG**

### **6.1.1 Study Drug Identification**

## GnRH agonist – Zoladex (goserelin)

## GnRH antagonist/GnRHa – Cetrotide (cetrorelix)

### **6.1.2 Study Drug Manufacturer**

## GnRH agonist - Zoladex

This will be supplied via the pharmacy and the maufacturer is Astra Zeneca.

## GnRH antag/GnRHa - Cetrotide

This will be supplied by the pharmacy and the manufacturer is MerckSerono.

### **6.1.3 Marketing Authorisation Holder**

The MA holder of Zoladex is Astra Zeneca (MA number PL17901/0064).

The MA holder of Cetrotide is Serono Europe Ltd (MA number EU/1/99/100/003).

### **6.1.4 Labelling and Packaging**

This study is not blinded. Both Zoladex and Cetrotide will be labelled and packaged as per the manufacturer’s supplied drug.

### **6.1.5 Storage**

Zoladex - Do not store above 25°C.

Cetrotide - Do not store above 25 °C. Keep the vial in the outer carton in order to protect from light.

### **6.1.6 Summary of Product Characteristics**

The Summary of Product Characteristics (SoPC) for each of the drugs is given in Appendix 1.

## **6.2 PLACEBO**

Not applicable

## **6.3 DOSING REGIME**

Pilot Group A GnRH agonist (Zoladex 3.6 mg subcutaneously monthly)

Pilot Group B No medication

Group 1 GnRH agonist only (Zoladex 3.6 mg subcutaneously monthly)

Group 2 GnRH antagonist (Cetrorelix 3 mg) given on 3 occasions ,day 1, 4+/- 1 day & 7+/- 1 day, commencing day 1 to 5 of the menstrual cycle, followed with GnRH agonist (Zoladex 3.6mg) thereafter monthly for 3 months, commencing day 7+/- 1 day.

Group 3 Control group – No medication

NB: Monthly is defined by 28 days +/- 3 days.

## **6.4 DOSE CHANGES**

There will be no dose changes during the study.

## **6.5 PARTICIPANT COMPLIANCE**

The drugs are administered in the clinic or in the patient’s home (except dose 1 cetrorelix)and refusal of dose will be recorded in the CRF.

## **6.6 OVERDOSE**

Since the drugs are physician administered the risk of overdose is low. In the event of overdose the manufacturer will be consulted.

## **6.7 OTHER MEDICATIONS**

### **6.7.1 Permitted Medications**

All other medications deemed necessary or standard of care are permitted.

### **6.7.2 Prohibited Medications**

There are no prohibited medications.

# **STUDY ASSESSMENTS**

## **7.1 SAFETY ASSESSMENTS**

There are safety assessments for -

Pilot Group A at Screening, Day 28+/- 3 days and on day of hysterectomy.

Pilot Group B at Screening and on day of hysterectomy.

Pilot Group C at Screening and on day of hysterectomy.

Groups 1 to 3 at Screening, Day 28+/- 3 days and on day of hysterectomy.

## **7.2 STUDY ASSESSMENTS**

See attached summaries of study plan at end of protocol (Appendix 4)

## **Sonographic assessment**

All patients will be asked to participate in the following study imaging assessments

### Transvaginal ultrasound [TVU] (and abdominal ultrasound [TAS], if necessary) to assess fibroid size and location. The volumes of the largest leiomyoma and the uterus will be measured based on an estimation of the volume of an ellipsoid (V=LDW/6 cm3) where L, W, and D represent length, width, and depth of the largest fibroid or the uterus.

### Subsequent scans (TVU / TAS) will be performed following start of medication at Visits 2, 3 and 4 (main study), Day 28+/- 3 days (Pilot Group A) and prior to hysterectomy (Pilot Groups A, B & C).and the same measurements will be carried out to record any changes from baseline.

## **7.2.2 Colour Doppler imaging**

To determine blood flow of the main uterine arteries colour Doppler imaging will be performed prior to the first study drug dose and repeated following start of medication at Visits 2, 3 and 4 (main study), Day 28+/- 3 days (Pilot Group A) and prior to hysterectomy (Pilot Groups A, B & C). Blood flow will be expressed using two impedance indices: the resistance index (RI) and the pulsatility index (PI). For each impedance index, the average of three measurements will be taken from the left and right arteries, respectively to enhance reproducibility.

## **7.2.3 Magnetic resonance (MR) imaging**

We aim to develop a novel non-invasive imaging protocol for serial examination of dynamic disease progression after therapeutic intervention (GnRH agonist, GnRH antagonist). Novel MR imaging strategies will include methods for characterisation of: uterine vascular density and perfusion; uterine fibroid volume; and assessment of cellular structure of fibroids.

Pilot Group A

Patients will be examined on 2 occasions:

##### (1) before commencing GnRH agonist (visit 1)

##### (2) just prior to hysterectomy(visit 2)

Pilot Group B

Patients will be examined on 1 occasion:

##### (1) just prior to hysterectomy(visit 2)

Pilot Group C

Patients will be examined on 1 occasion:

(1) just prior to hysterectomy (visit 2)

Main Study

##### Clinical MR imaging will be performed. Patients will be examined on four occasions:

##### (1) before commencing GnRH agonist, GnRH antagonist therapy (visit 1);

##### (2) after 14 days+/- 3 days (visit 2);

##### (3) after 28 days +/- 3 days (visit 3);

##### (4) within 10 days prior to hysterectomy(visit 4)

Pre- and post GnRH agonist / GnRH antagonist treatment and control subjects will undergo breath-hold fast-spin-echo T2-weighted imaging acquired in planes oblique to the uterus, magnetization transfer, contrast-enhanced T1-volume scans and dynamic contrast imaging using a phased array torso coil on MR scanner.

Dynamic contrast imaging will use T1-weighted SPGR scans acquired at a number of time points after injection of gadolinium, e.g.  = 0, 30, 60, 90, 120 180, 240 and 300 seconds (Have practical limits in that patients usually become restless after about 30-40 minutes in MRI). Development work will be required to determine the optimum number and temporal resolution for this imaging to allow analysis of fibroid perfusion and permeability. Subjects will be carefully positioned so that the scan locations are as close as possible between pre- and post-treatment examinations. The use of image registration methods, such as FLIRT (www.fmrib.ox.ac.uk/fsl), to allow further fine alignment of imaging data will be investigated.

Uterus and enhancing and non-enhancing fibroid volumes pre- and post treatment will be determined from the T2- and T1-weighted structural scans using ANALYZE (Mayo Foundation, Rochester, MN, USA). Reduction in uterus and fibroid volumes will be determined as 100  (Volpre – Volpost)/Volpre.

Uterine and fibroid vascular density will be determined from signal-time curves generated from the dynamic contrast imaging data. Following the protocol described by Jha et al. (2000)10, regions-of-interest (ROI) will be placed over fibroids and a control region, for example myometrium, and signal-time curves produced. The ratio of fibroid to myometrrium signal intensity will then be calculated for each of the time points , and the maximum value determined. This maximum ratio value will then be used to determine the effect of treatment on fibroid vascularity from the relation 100  (Ratiopre – Ratiopost)/Ratiopre. The application of image analysis protocols developed in the SFC Brain Imaging Centre, University of Edinburgh, to measure perfusion and permeability parameters from signal-time curves in brain tumours, will also be investigated in fibroids13.

Finally, we will investigate whether magnetisation transfer MRI (MTI) can provide a non-invasive biomarker to measure the clinical response of fibroids to treatment. This imaging modality provides an index, the magnetization transfer ratio (MTR), which measures the efficiency of the magnetization exchange between the relatively free water protons inside tissue and those bound to protein macromolecules in cellular membranes. We hypothesise that any pathological change in fibroid structure that involves alterations to cellular membrane macromolecules will change MTR and thus differentiate fibrous from normal tissue. We have previously used this technique to investigate the effects of ageing on the brain’s white matter11.

Development work will be required to determine the optimum imaging sequence parameters to provide MTI contrast in the uterus.

The examination of the uterus will include examination in the Preclinical Magnetic Resonance Imaging Unit (situated in the University of Edinburgh, Chancellors Building, at Little France site) using a 7T scanner. The inner diameter of the coil is 15cm thus able to accommodate the uterus once removed at hysterectomy. High resolution scans (T1W, T2W and MTI) will be carried out for comparison with histology.

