# **INTRODUCTION**

## **1.1 BACKGROUND**

Complaints of excessive blood loss impose a detrimental impact on quality of life for healthy women1. Annually in the UK 3.5 million workdays are lost2 and treatment costs for menstrual complaints exceed £65m. Heavy menstrual bleeding (HMB; menorrhagia) is by far the most common complaint in women with symptomatic uterine fibroids (also termed leiomyomas), and represents the major indication for surgical intervention (hysterectomy).

Fibroids may be present in as many as 80% of women of reproductive age. One in 4 Caucasian women report clinically significant symptoms attributable to the presence of fibroids. Prevalence peaks in the perimenopausal years. Obesity and an early menarche are known risk factors, likely due to the increased lifetime exposure to oestrogen3. The mechanism of HMB in women with fibroids is not understood.

To date there are no approved medical treatments for long-term management of women with symptomatic fibroids.

Current treatments for fibroids are surgical or invasive in nature. Surgical removal (myomectomy) and hysterectomy are mainstays of management. Uterine artery embolisation (UAE) was introduced ten years ago as an alternative to hysterectomy for the surgical management of fibroids. The efficacy of UAE as an alternative therapy to surgery for uterine fibroids has recently been demonstrated to require longer-term follow-up4.

GnRH-analogues are used for medical treatment of symptomatic uterine fibroids pre-surgery. After 3-6 months of treatment, the resultant hypo-oestrogenic state results in an average 20-50% decrease in uterine and fibroid size5. It is assumed that it is the hypoestrogenism that causes shrinkage of fibroids; however addition of tamoxifen actually increases fibroid growth6. Much of the shrinkage occurs in the first 2 weeks when the women are not hypoestrogenic. The immediate suppression of the pituitary achieved with GnRH antagonists, with no initial stimulatory effect is the main advantage over the GnRH agonists. GnRH antagonists have been developed with acceptable pharmacokinetic and safety profiles7 and use proposed for management of fibroids.

There is unmet need for a pharmacologic agent able to reduce excessive bleeding and other symptoms associated with increased uterine volume, which could prevent or significantly delay surgery without causing significant unwanted hypoestrogenic side effects and allow preservation of fertility.

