### aged >18 years.

### Scheduled for hysterectomy with a fibroid uterus

### At least one intramural non-pedunculated, submucosal or subserous fibroid with a diameter of  2cm or multiple small fibroids with a uterine volume of  200cm3 confirmed by transvaginal or abdominal ultrasonography

### Normal cervical cytology within 3 years.

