# **STATISTICS AND DATA ANALYSIS**

## **9.1 SAMPLE SIZE CALCULATION**

No sample size required for pilot group.

Sample size calculations for this sort of study are very difficult. This is a hypothesis generating study, and findings will need to be confirmed in a separate larger study. A sample size of 10 patients in each group will give an 80% power, at a significance level of 5%, to detect a difference in the change in volume of 160cm cubed (s.d of change in volume = 120cm cubed) between a treated group and the control group. This calculation does not take multiple comparisons into account.

In terms of agreement 30 subjects would allow us to estimate limits of agreement +/- 0.6 standard deviations of the difference between measurements using Bland-Altman methods.

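### Volume response appears on three scales (percentage reduction in 7.2.3, cm³ change in 9.1, raw pre-hysterectomy volume in 9.2), and the stated 80% power applies only to the second

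*Protocol*

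**What the plan says.** Four places in the protocol bear on the scale of the volume response.

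- **7.2.3, MR imaging:** "Reduction in uterus and fibroid volumes will be determined as 100" × (Volpre – Volpost)/Volpre. This is a percentage of each woman's own pre-treatment volume, for both uterus and fibroid.
- **9.1, sample size:** "A sample size of 10 patients in each group will give an 80% power", at 5% significance, "to detect a difference in the change in volume of 160cm cubed", with an SD of the change of 120 cm³. This is an absolute change, treated group against control. The organ is not named.
- **9.2, primary analysis (1):** uterine volume just before surgery is compared between treated and control women by t-test or a rank equivalent. Neither change, nor percentage, nor baseline volume is mentioned.
- **1.1, background:** the expected effect is given only as a percentage: "the resultant hypo-oestrogenic state results in an average 20-50% decrease in uterine and fibroid size".

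No section gives a mean or SD of baseline volume, or an SD of percentage change.

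**The concern.** The three quantities are percentage reduction, cm³ change and raw follow-up volume. They answer different questions and have different variances. A power figure derived for one says nothing about another without the baseline distribution, which the protocol does not supply.

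Two things are at stake. First, a reader will take 80% as the power of the primary comparison, although the comparison named in 9.2 is not the one that was sized. Second, with 10 women per arm, significance can depend on the scale. If the protocol does not say which one counts, the choice can be made after the data are seen.

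**Working it through.** **1. Reproduce the stated figure.** Inputs from 9.1: n = 10 per group, difference 160 cm³, SD 120 cm³, alpha 5% (sidedness not stated; two-sided taken).

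Noncentrality = 160 / (120 × √(2/10)) = 160 / 53.67 = 2.98. The critical t on 18 df is 2.101. Power from the noncentral t is **80.5%**, so 9.1 is correct for absolute change.

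**2. What 160 cm³ means as a percentage.** 160/0.50 = 320 and 160/0.20 = 800. The 9.1 effect therefore matches the 20–50% range in 1.1 only if mean baseline volume lies between 320 and 800 cm³. The documents do not say whether it does.

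**3. Power of the comparison named in 9.2.** The relevant SD is now the between-woman SD of follow-up volume, which is not given. For a 160 cm³ difference, 10 v 10:

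| Assumed SD of follow-up volume (cm³) | Power |
|---|---|
| 120 | 80% |
| 150 | 62% |
| 200 | 40% |
| 250 | 27% |
| 300 | 20% |

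The 80% survives only if women differ from one another at follow-up no more than their changes differ.

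**4. Power on the percentage scale.** Simulation, 20,000 trials per setting. Assumed: lognormal baseline with mean 400–800 cm³ and CV 0.3–0.7, mean effect 160 cm³, and SD of cm³ change held at 120 (pooled over arms in the proportional case).

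| Shrinkage mechanism | Absolute change | Percentage reduction |
|---|---|---|
| Additive in cm³ | about 80% | 61–76% |
| Proportional to baseline | 82–90% | 86–99.6% |

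The error can go either way, and the documents do not settle which.

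**5. How often the scales disagree.** Second simulation, 20,000 trials per setting. Assumed: lognormal baseline, mean shrinkage 20% in the treated arm and none in control, SD of percentage change 15 points treated and 10 points control. Baseline means of 320, 457 and 800 cm³ give the same picture.

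| Baseline CV | Absolute change | Percentage | Disagree on p<0.05 | Raw follow-up volume (9.2) | Log volume adjusted for log baseline |
|---|---|---|---|---|---|
| 0.4 | 85–86% | 91% | 8% | 20% | 89–90% |
| 0.6 | 78% | 91% | 15% | 12% | 89–90% |
| 0.8 | 70% | 91% | 22–23% | 8–9% | 89–90% |

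At 35–50% shrinkage the absolute and percentage tests both reach about 95% or more and disagree in at most about 5% of trials.

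**The case against.** Several points can fairly be made for the protocol.

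- Section 7.2.3 describes image measurement and does not call the percentage the primary analysis variable. The primary endpoint is feasibility and reproducibility of MR, and 2.2.2 says no efficacy measurement is needed. This lowers the stakes. But 9.2 still lists a between-group volume test as a primary analysis and 9.1 states a power, so the mismatch remains.
- Section 9.2 allows a non-parametric test. With the step 5 assumptions, a rank test on absolute change has 84%, 80% and 77% power at CV 0.4, 0.6 and 0.8. That recovers part of the loss in the cm³ test at high CV. It does not reconcile the scales.
- The study is described as hypothesis generating, and 9.2 limits itself to descriptive statistics. That supports a modest severity.
- The choice of model could be left to an analysis plan. A power statement that does not match the named primary comparison is, however, in the protocol itself.

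Some stronger readings are tempting but not supported.

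- *The 80% is miscalculated.* It is not; see step 1.
- *Section 7.2.3 assumes proportional shrinkage.* Expressing a change as a percentage makes no such assumption.
- *Power collapses in small uteri near an entry volume of 200 cm³.* In 4.2 that threshold belongs only to the alternative worded "or multiple small fibroids with a uterine volume of"; a woman with one qualifying fibroid enters with no stated uterine volume. A loss of power would also require the SD to stay at 120 cm³ in a 200 cm³ uterus. With the step 5 SDs it would be 30 cm³ treated (15% of 200) and 20 cm³ control (10% of 200), and a 40 cm³ fall would have about 91% power.
- *The percentage scale is the more powerful one.* That holds under proportional shrinkage and reverses under additive shrinkage.

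**Conclusion.** The point holds as an inconsistency of scale. The 80% belongs to absolute change in cm³ and to nothing else in the protocol. It does not describe the percentage response in 7.2.3. Nor does it describe the follow-up-only comparison in 9.2, which is the more consequential gap: power there falls from 80% to 20% as the assumed SD of follow-up volume rises from 120 to 300 cm³.

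For the percentage scale, neither the size nor the direction of the error can be fixed from the documents. The disagreement of about 8–23% between scales rests on an assumed lognormal baseline, CV 0.4–0.8, 20% proportional shrinkage and the stated percentage SDs. It largely disappears at 35–50% shrinkage. The matter should be corrected, but no confirmatory claim depends on it.

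**What to change.** Use one scale in 7.2.3, 9.1 and 9.2. One suitable choice is to analyse log pre-hysterectomy volume with log Visit 1 volume as covariate, and to back-transform the group difference to a percentage reduction, in line with 7.2.3. Restate 9.1 as the detectable effect on that scale, with the assumed SD and its source. Report the cm³ change descriptively.

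No new measurement is needed, because Visit 1 and Visit 4 volumes are already planned. The cost is wording and a re-derived power statement. The drawback is that the SD on the new scale has to be assumed. Pilot Group A is scanned before and after treatment, so it can supply a treated-arm value. Pilot Groups B and C have a single MR examination occasion, so no pilot group gives a control-arm SD of change. The restated power should therefore be shown over a range of SDs.

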## **1.2 RATIONALE FOR STUDY**

The purpose of this study is to investigate and validate the potential use of structural, dynamic contrast and magnetization transfer MR imaging as a non-invasive biomarker for monitoring responses to medical interventions aimed at reduction of excessive menstrual bleeding and decrease in uterine/ fibroid volume.

Such MR imaging strategies should provide a method to visualize and quantify changes in:

1. uterus and fibroid volume;
2. uterine vascular density and perfusion;
3. vasculature and extracellular matrix content of fibroids -

in women with fibroids administered a gonadotrophin-releasing hormone agonist (GnRH-a), either alone or with initial administration of a GnRH antagonist, for adjunct therapy to reduce uterine bleeding prior to hysterectomy.

The proposed study design will also provide important mechanistic information on whether the reduction in blood flow of uterine/ fibroid vasculature and shrinkage of fibroids is dependent upon subjects being hypoestrogenic.

Comparisons of novel magnetic resonance imaging data of the fibroid uterus, pre- and post GnRHa, GnRH antagonist, with a comparative “control” group of women who receive no therapeutic intervention pre-hysterectomy, will be made.

We will employ (1) routine ultrasound and colour Doppler imaging techniques; (2) use MR imaging and explore a novel “pre-clinical” opportunity to examine ex-vivo 7T imaging and correlate imaging data with the histo/morphology of uterine specimens; and (3) undertake histo-morphology of the uterus removed at hysterectomy. We will evaluate whether imaging with MR is applicable for the study of modulation of morphology and cellular arrangements of tissue and vascular structures in the uterus, thereby informing mechanism of action of therapies.

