### **2.2.2 Secondary Endpoints**

1. Uterine vascular perfusion

1. Vasculature and extracellular matrix (ECM content of fibroids)

3. Whether (a) reduction of blood flow of uterine and fibroid vasculature and (b) shrinkage of fibroid depends upon subject being hypoestrogenic.

NB. The study aims to establish feasibility and reproduce ability of novel MR imaging techniques in the evaluation of treatment response in women with uterine fibroids. Hence there is not an efficacy measurement required for any of the drug treatment options.

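### The MR vascularity index divides fibroid signal by the signal of a tissue that may itself respond to treatment, without baseline correction, so it can understate, cancel or reverse a fibroid effect

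*Protocol*

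**What the plan says.** Protocol Section 7.2.3 opens its account of the dynamic contrast data with a promise covering two tissues: "Uterine and fibroid vascular density will be determined from signal-time curves generated from the dynamic contrast imaging data". The method is then set out in order:

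- Regions: "regions-of-interest (ROI) will be placed over fibroids and a control region, for example myometrium, and signal-time curves produced". Myometrium is named here as an example, but the next sentence makes it the denominator of the ratio.
- Ratio: the fibroid-to-myometrium "signal intensity will then be calculated for each of the time points", and the maximum is found.
- Effect: "This maximum ratio value will then be used to determine the effect of treatment on fibroid vascularity", as 100 × (Ratio pre − Ratio post)/Ratio pre.

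The example acquisition times are "0, 30, 60, 90, 120 180, 240 and 300 seconds" after gadolinium. Their number and spacing are left to development work. No subtraction of pre-contrast signal is stated, and no time point is excluded from the maximum.

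Elsewhere the protocol treats the uterus as a possible responder. Section 1.2 asks "whether the reduction in blood flow of uterine/ fibroid vasculature and shrinkage of fibroids is dependent upon subjects being hypoestrogenic". Secondary endpoint 3 (Section 2.2.2) concerns "reduction of blood flow of uterine and fibroid vasculature". Section 7.2.4 examines the myometrial as well as the leiomyoma compartment for response to medication. Uterine vascular perfusion is secondary endpoint 1, with its own analysis in Section 9.2.

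**The concern.** A reference region does its job only if treatment leaves it alone. Here the reference tissue receives the same systemic drug and belongs to the organ whose blood flow is under study. If both tissues lose enhancement, the ratio removes some or all of the change. If myometrium loses more, the ratio rises and the fibroid appears more vascular after treatment.

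Two further features add to this. The ratio uses signal rather than enhancement, so the unenhanced signal in numerator and denominator dilutes any change. And a maximum over a set that contains 0 s can never be lower than the ratio at 0 s, which is in effect the pre-contrast ratio and says nothing about vascularity.

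The ratio also yields one number about fibroid relative to myometrium. It gives no separate measure of uterine vascularity, although the section says both will come from these curves.

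The study exists to judge whether MR techniques can serve as biomarkers of response. An insensitive or sign-reversing index could make dynamic contrast imaging look uninformative, or fibroid vascularity look unresponsive, because of the formula rather than the tissue.

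**Working it through.** The protocol gives no figure for this index and no enhancement values, so there is no stated number to reproduce. The formula was evaluated directly.

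**From Section 7.2.3:** R(t) = fibroid signal/myometrial signal; index = 100 × (max R pre − max R post)/max R pre; times 0, 30, 60, 90, 120, 180, 240 and 300 s.

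**Assumed, for illustration only:** equal unenhanced signal in the two tissues, so R(t) = (1 + E_F(t))/(1 + E_M(t)); enhancement rising exponentially with a 45 s time constant; pre-treatment plateau enhancement of 1.0 in myometrium and 1.5, 1.0 or 0.6 in the fibroid; treatment scaling the plateaus down.

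**Cancellation, at the plateau with a fibroid of 1.5.** Before treatment R = 2.5/2.0 = 1.25.

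- Both fall 50%: R = 1.75/1.50 = 1.167; index = 100 × (1.25 − 1.167)/1.25 = 6.7%.
- Fibroid falls 25%, myometrium 50%: R = 2.125/1.50 = 1.417; index = −13.3%, the wrong sign.
- Fibroid falls 20%, myometrium stable: R = 2.2/2.0 = 1.10; index = 12.0%. The direction is right, but a 20% fall in enhancement reads as 12% because the unenhanced signal is still in the ratio.

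**Floor.** Since max R ≥ R(0), and R(0) = 1 here, the post-treatment value cannot go below 1. With a fibroid of 1.5 and stable myometrium, falls of 50% and of 80% both give 100 × (1.25 − 1.00)/1.25 = 20.0%.

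**Results over the full time course:**

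| Fibroid plateau before treatment | Fall in enhancement, fibroid / myometrium | Index with 0 s | Index without 0 s |
|---|---|---|---|
| 1.5 | 20% / 0% | 12.0% | 12.0% |
| 1.5 | 50% / 0% | 20.0% | 26.5% |
| 1.5 | 80% / 0% | 20.0% | 38.3% |
| 1.5 | 50% / 50% | 6.7% | 6.7% |
| 1.5 | 25% / 50% | −13.3% | −13.3% |
| 1.0 | 50% / 0% | 0.0% | 16.4% |
| 1.0 | 80% / 0% | 0.0% | 26.2% |
| 1.0 | 50% / 50% | 0.0% | 0.0% |
| 0.6 | 50% / 0% | 0.0% | 11.3% |
| 0.6 | 50% / 50% | 0.0% | −6.1% |

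Dropping 0 s removes the floor at the pre-contrast ratio but not the cancellation. Where the fibroid enhances less than myometrium throughout, the maximum then sits at 30 s, the earliest remaining point.

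**The alternative on the same curves.** With (S(t) − S0)/S0 in each tissue, a 50% fall in fibroid enhancement takes the 1.5 plateau to 0.75 and reads as 50%, whatever myometrium does. Myometrium gets its own figure.

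**The case against.** Four objections have weight.

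*The effects are conditional.* A reader might infer that the index always cancels or floors the treatment effect. The documents do not support that. They ask whether uterine flow falls; they do not say that myometrial enhancement falls, or by as much as fibroid enhancement, which full cancellation needs. The floor matters only when the fibroid enhances relatively no more than myometrium at every sampled time, before or after treatment; a fibroid that enhances early but peaks lower can still have its maximum after contrast. The 12.0% row shows the index working. This objection stands and limits the claim to what can happen.

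*The 0 s point is not fixed.* It is in an example list open to development work, and Section 3.1 uses the pilot groups to refine perfusion imaging. This also stands, though the ratio is stated for each time point and nothing excludes the first.

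*Other vascular measures exist.* A reader might infer that the perfusion endpoint and the mechanistic objective rest on this index. They do not. Section 7.2.2 measures uterine artery impedance by Doppler, and Section 7.2.3 also plans enhancing and non-enhancing fibroid volumes and will investigate perfusion and permeability parameters. The ratio is applied only to fibroid vascularity, and the analysis is secondary, descriptive and hypothesis-generating (Sections 9.1 and 9.2). This lowers the stakes. It does not repair the formula: Doppler covers the main uterine arteries rather than tissue, and the perfusion and permeability parameters have no stated derivation.

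*The method follows a published protocol.* How that source handles baseline signal cannot be checked here. The point therefore concerns the formula as this protocol writes it.

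**Conclusion.** The point holds as a weakness of a secondary measure. As written, the index has a denominator that the protocol itself regards as a possible responder, uses signal without baseline correction, and does not keep a pre-contrast point out of the maximum. It can therefore attenuate, cancel or reverse a fibroid effect and, if 0 s is retained, cannot register a fall below the pre-contrast ratio. It also leaves uterine vascularity without a measure of its own from these curves; this part does not depend on how either tissue enhances.

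The size cannot be obtained from the documents. Under the assumptions shown, 50% falls in both tissues give 6.7%, 0.0% and 0.0% with 0 s kept (fibroid plateaus 1.5, 1.0 and 0.6), and a larger myometrial fall gives −13.3% (fibroid plateau 1.5). These figures illustrate the mechanism and do not predict this trial's results. With stable myometrium and a fibroid that stays brighter, the direction is right. The change is worth making because it is cheap; the trial's primary analyses are not affected.

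**What to change.** In Section 7.2.3, using the same regions of interest and signal-time curves:

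1. Derive relative enhancement (S(t) − S0)/S0 separately for fibroid and for myometrium, with S0 the pre-contrast signal of that tissue in that scan.
2. Use the two results as the MR measures of fibroid and of uterine vascularity.
3. Keep the pre-contrast image as the source of S0, but exclude it from any maximum over time.
4. Report the fibroid-to-myometrium ratio alongside as a descriptive comparison with the cited method.

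The cost is a little extra derivation; no additional scans or regions are needed. The real loss is the normalisation between scans that a within-scan ratio provides, which reporting the ratio alongside mitigates. A reference tissue outside the uterus could be added if a ratio is still wanted, but that is optional, and the documents do not show that any such tissue is stable under treatment.
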